**S. 1. Background:**

With a globally growing number of smokers, up to about half of men and one tenth of women are becoming smokers and relatively few stopping [1, 2]. The global smoking report presents that most of smokers live in middle- and low-income countries including China, where the availability of smoking cessation service is scarce [3].

There is evidence that tobacco is responsible for even more deaths and diseases [3]. The number of deaths attributed to tobacco use has reached 1.2 million per year, whereas the death toll is expected to rise to 2 million annually by 2025 [4]. Smokers have two to three times mortality in middle age among otherwise similar persons who had never smoked [3]. The smokers that still live in middle age also have lost at least a decade of life time, because the tobacco is also the biggest external cause of non-communicable disease [5]. According to the literature review, smoking has been confirmed to be an important risk factor to coronary heart disease, chronic obstructive lung disease, cancer, stroke, peptic ulcer, peripheral vascular disease, aortic aneurysm, osteoporosis, low bone density, cataract, pneumonia, periodontitis, subclinical arteriosclerosis[6, 7]. In addition, tobacco can also increase the incidence rate of cancer in lung, oral cavity, naso-, oro- and hypopharynx, nasal cavity and accessory sinuses, larynx, oesophagus, stomach, pancreasm colorectum, liver, kidney ureter, urinary bladder, uterine cervix and ovary, and myeloid leukemia, among smokers [8-10].

However, the impact caused by tobacco is far more than that. For the male smokers at their reproductive ages, who is preparing to have a baby, smoking may negatively influence their reproductive capacity. Sufficient studies found that the quantity and duration of smoking, especially the current smoking is positively associated with the risk of erectile dysfunction[11, 12]. The clinical study provided strong indirect evidence that smoking may affect penile erection by the impairment of endothelium dependent smooth muscle relaxation. The association of erectile dysfunction with risk factors such as coronary artery disease and hypertension appears to be amplified by cigarette smoking[13]. Besides, the quality and quantity of sperm of smokers were lower than that of non-smokers. Even though, the mechanism is not clear, many research results has reported that smokers had a significant decrease in the semen volume, and rapid progressive motility and sperm viability [14, 15]. Moreover, smokers had a significant increase in the levels of immotile sperms and semen leukocytes. Sperm motion parameters were all lower in the smokers [16]. Further, the percentage of abnormal morphology sperm was significantly more than their non-smoker counterparts[17]. What's worse, the sperm morphology was worse with increasing degree of smoking [14, 18]. All

stated above means that smoking may increase the risk of a higher risk of developing oligospermia, asthenozoospermia and teratozoospermia for man in the reproductive years[15], which may lead to the inefficiency of fertilization and even give birth to abnormal fetus. According to the official report, more than half of males are smokers in mainland China [4]. In addition, half of them have been smokers before 20 years old [16]. That means there are a large among of male smokers are under the hazard of smoking.

Excepting for the impact on reproductive male smokers their own, Secondhand Smoking (SHS) exposure also has further and longer negative effects on their female partners and their babies born in the future. A cross-countries study showed that median air nicotine concentration was 17 times higher in households with smokers compared with households without smokers. However, it is widely admitted that there is no risk-free level of exposure to the SHS. The non-smoking population is much more sensitive to the nicotine in the passive smoking than smokers [17, 18]. The SHS may increase the risk of respiratory infections, ear problem, immediate adverse effects on cardiovascular system, CHD, lung cancer and so on to adults [19]. For children, the passive smoking takes children a higher chance to get severe asthma, slow lung growth. Hence, children and women live with smokers may have a higher risk of premature death and disease [20]. Moreover, the harm of SHS to the unborn fetus and newborn babies of male smokers is worse, even lethal. When compared with non-smoking women with no SHS exposure, non-smoking women with SHS exposure reported to have more proportion of spontaneous abortion, stillbirth, tubal ectopic pregnancy, preterm birth, and high risk of very preterm birth increased with the duration of exposure [21-23]. Plenty of research found that ETS exposure was also reported to be associated with an increased risk of aplasia, in which low birth weight was reported mostly [24]. Besides, newborns whose mothers were exposed to secondhand smoke showed significantly lower scores in the habituation cluster and motor system cluster [25], as well as the delay of neurobehavioral development regardless of socio-demographic, obstetric and pediatric factors [26]. Conclusionly, smoking has direct and indirect negative effect to male smokers in reproductive ages themselves and their family members. Therefor, finding solutions for this problem is extremely urgent.

So far, quitting smoking is the only proven efficient routine to essentially solve this problem. Several studies consistently concluded that persons who began smoking in early adulthood but stopped before 40 years of age avoid more than 90% of the excess risk during their next few decades of life, as compared with those who continue to smoke, and even those who stop at 50 years of age avoid more than half the excess risk [27-29]. What's more, the exposure dose to pregnant women and children has been proven to be partly associated with the negative impact above [30].

A global statistics review showed that there has been widespread cessation in many high-income countries, however, quitting is uncommon for smokers in China [3]. Based on the official statistic figures in 2010, about one third of people in China were current smokers, and the number of young smokers is increasing [4]. While most current smokers (83.9%) report having no intention

to quit smoking [31]. On average, between 60% and 70% of Chinese men continue to smoke into middle age, which is different with the western countries. [32]. Another reports in 2005 and 2010, respectively, indicated that about 74% and 84% of smokers did not want to quit or never thought about quitting[33, 34]. Approximately 20% to 25% of smokers had attempted to quit at least once, but about half relapsed [4]. Noteworthily, a global comparison report shows that the estimated age-standardized prevalence of daily smoking among male smokers and female smokers in China is located in the highest and lowest deciles around the world, respectively [35]. According to the global statistic data, the secondhand smoking(SHS) exposure of non-smoking children and females is ranged from 17.3% to 73.1% inside home[36-38]. In China, this average rate was around 60%, the highest one has reached to 82.5% in large cities [4, 39, 40]. We can infer from the data above that a large amount of men is smoking and a great number of women are suffering from the damage of second hand smoking in China. Hence, finding out a solution to decrease the married reproductive male smoking rate is extremely crucial.

Based on surveys conducted in China, excepting for the sociocultural factors favouring smoking initiation, lack of awareness the hazards of smoking, and weak social support are mainly responsible for the low rate of smoking cessation for male individuals in China [41, 42].

Overall awareness of the health hazards of tobacco has improved in the last 15 years in China, but is still relatively poor [43]. Yang and his colleagues found that over 80% of the males was aware that smoking causes serious diseases but over half of these people can not identify what kinds of disease can be caused by smoking. Less than two thirds of males were aware that secondhand smoke can cause serious diseases. Besides them, only small part of people considered that secondhand smoking can cause serious impact on children [43]. Even there were several patterns of propaganda and education applied in China, the efficiency is not very satisfactory. Lacking of motivation was the main explanation for the low smoking cessation rate. In China, parents' high attention on the children is general. Hence, emphasizing the health hazards of tobacco to male smokers and secondhand smoking to their wives and baby born in the future shoule probabliiy be a effective motivation for reproductive male smokers in China.

Besides, belief in the ability to control the health effects of smoking is another barrier of smoking cessation for Chinese male smokers on the individual level [44]. Self-efficacy is the belief that one has the power to produce that effect by completing a given task or activity related to that competency [45, 46]. Generally, quitting smoking is well recognized to positively associated with the smoking cessation[47, 48]. It influence the smokers' thought patterns and emotional reactions. High self-efficacy helps create feelings of serenity in approaching difficult to quit smoking. Converging evidence from diverse methodological and analytic strategies verifies that perceived self-efficacy and personal goals enhance motivation and performance attainments[49]. When self-efficacy belief and outcome expectation differ, the self-efficacy belief is more likely to determine the behavior[50]. That means a high self-efficacy may indicate a high possibility to change to quit

and a less chance of relapse for smokers [47]. Thus, enhance the self-efficacy of changing for male smokers is a crucial steps to quitting smoking. Previous research found that, providing information and knowledge related to how to change can improve the self-efficacy of behavior changing[51]. By understanding how to change and coping with the negative physical and psychological reactions, the smokers will be more confident to the smoking cessation. Besides, social support, especially the family support, can also enhance the smokers' self-efficacy related to smoking cessation [52, 53]. By maintaining a positive regard and provide psychological decompression for the smoker, supportive family may motivates the smoker for quitting smoking[54]. Hence, improving the information and communication to increase the knowledge of the adverse impact of smoking on the smokers, family members and their baby born in the future to male smokers and their family members especially their wives, is an important way to enhance their motivation to quit smoking. Future smoking control initiatives that target non-smoking women to influence male smoking should take into account the women's overarching need to maintain the status and harmony of their families[55]. To sum up, useful information and family support can help to enhance the self-efficacy, and further promote the behavior of quitting smoking for male smokers[56].

Different patterns of interventions, such as counselling, advertising, leaflets and so on have been implemented, however the effect is not so well as we expected. Thus, a more efficient intervention should be developed. As the high usage rate of smartphone, interventions implemented by cellphone can be considered as a new approach. Watching video has been proven to be significantly associated with prevalence abstinence [53]. Feedback from participants indicated that the support provided by the video role models was important and appreciated. In a multiple intervention medium, the text is fast and precise, but it's also impersonal and monotonous to interpretation without tone; voice can express inflection and need less attention, but easy to miss information; images can stimulate the visual power and improve the delights, however, it has limits to delivery information. Video, combining with the advantage of text, image, and tones, will take visual, auditory and reading stimulation to the brain, consequently, enhance the delivery and memory of information for people. Hence video is an efficient intervention medium for smoking cessation[57].

Cigarette can negatively influence the function of respiratory, urinary and other systems, as well as increase the risk of different types of cancer. The secondhand smoking is harmful to their family members. What's worse, the impact of reproductive system will further damage their baby born in the future. For Chinese people, the high prevalence and low quitting rate made this situation much worse. In addition, as the cancel of one-child policy, lots of couples are planning to give birth to baby in the future decades compared with the period the policy was valid. Hence, an intervention should be urgent to be applied to help male whose partners got pregnant to quit or reduce the cigarette smoking. Hence this study aims to

- (1) Measure the smoking consume of male smokers whose partner got pregnant,

(2) Developing a media-led intervention to help these male smokers whose partner got pregnant,

(3) To detect the effectiveness of the media-led intervention for the male smokers whose partner got pregnant.

## **S. 2. Theoretical framework:**

A risk communication approach guided by the theory of planned behavior (TPB) will be used in this study. The TPB is a theory that links beliefs and behavior proposed by Icek Ajzen to improve on the predictive power of the theory of reasoned action by including perceived behavioural control[58]. It has been applied to studies of the relations among beliefs, attitudes, behavioral intentions and behaviors in various fields such as public relations, healthcare, as well as smoking cessation in recent years[59].

The theory states that attitude toward behavior, subjective norms, and perceived behavioral control, together shape an individual's behavioral intentions and behaviors. If people evaluate the suggested behavior as positive (attitude), and if they think their significant others want them to perform the behavior (subjective norm), this results in a higher intention (motivations) and they are more likely to do so. A high correlation of attitudes and subjective norms to behavioral intention, and subsequently to behavior, has been confirmed in many studies.

However, because of circumstantial limitations, behavioral intention does not always lead to actual behavior. Namely, since behavioral intention cannot be the exclusive determinant of behavior where an individual's control over the behavior is incomplete. Hence, perceived behavioral control was induced. Perceived behavioral control, refers to the degree to which a person believes that they control any given behavior (class notes). The theory of planned behavior suggests that people are much more likely to intend to enact certain behaviors when they feel that they can enact them successfully. Increased perceived behavioral control is a mix of two dimensions: self-efficacy and controllability. Self-efficacy, which was proposed by Bandura in 1977 in the social cognitive theory, refers to the level of difficulty that is required to perform the behavior, or one's belief in their own ability to succeed in performing the behavior. Controllability refers to the outside factors, and one's belief that they personally have control over the performance of the behavior, or if it is controlled by externally, uncontrollable factors. If a person has high perceived behavioral control, then they have an increased confidence that they are capable of performing the specific behavior successfully.

As shown in figure 1, a risk communication approach will be used to deliver the hazard of smoking to the health and unborn baby to participants to increase the attitude towards quitting and subjective norm. Combining with the increasing of the two factors, the participants' intention to quit will enhance, and finally prompt the participants to quit smoking.

Figure 1. The theoretical framework of smoking cessation based on the Heath Belief Model.

[figure not shown]

### S. 3. Methodology

#### S. 3.1. Phase 1: Video developing

##### S. 3.1.1. Study Design

Before the intervention is implemented, a set of videos delivering the hazard of smoking will be developed. In this phase, four 1-minutes video will be produced that presented the health effects of smoking, especially emphasizing the importance of smoking cessation on the fetal and pregnancy. These videos will be drafted and then framed by the research staff.

##### S. 3.1.2. Evaluation

To holding subjects' interest, both static and dynamic pictures as well as short video clips will be used. The visuals will match and synchronize with the content of the auditory presentation to create coherent loss and gain. Auditory and visual materials will be produced professionally to optimize their quality. Finally, these videos will be evaluated by 3 healthcare professionals in this field before sending to the participants by smartphone stage by stage [57].

#### S. 3.2. Phase 2: Pilot study

##### S. 3.2.1. Study Design

Before the formal intervention is implemented, a pilot study will be applied to test the feasibility and acceptability of the video-led intervention.

##### S. 3.2.2. Sampling

Respectively 10 male smokers in Shenzhen who met the inclusion criteria for the study will

be invited to participate in this study. The inclusion criteria are: the participants should be (1) male resident aged 18 or above; (2) smoking at least one cigarette per day averagely during the past 3 months; (3) get married and partner has been pregnant; (4) able to communicate in Mandarin (including reading Chinese); and (5) have a smartphone for intervention and follow-up. Smokers who meet the above criteria but are currently involved in other smoking cessation programs and/or mentally or physically unfit for communication will be excluded.

### **S. 3.2.3 Measurement**

#### *S. 3.2.3.1. Demographics information sheet*

The participants will be collected by using a self-designed demographics information questionnaire. The content of the demographics information sheets will include the age, gender, occupation, family income, education level, marriage status, the situation of child, the intend of pregnancy, patterner of smoking status, medical history, and alcohol using.

#### *S. 3.2.3.2. Smoking characteristics*

The baseline of smoking characteristics of the participants will be collected through a simplified questionnaire set which includes levels of daily cigarette consumption, history of past quit attempts.

#### *S. 3.2.3.3. Structured interview*

A ten minutes structured intervention aims to obtain the feasibility and acceptability of these videos will be applied to these participants. The interview will follow an outline about the evaluation and understanding for the vedios. The outline of the interview has been list in the table 1.

Table 1. Outline of structured interview for the feasibility and acceptability of video intervention.

- 
1. Can you revieve the videos successfully or not? Please indicate the problems you faced during the video receiving.
  2. Can you watch the videos smoothly or not? Please indicate which part or the possible reason that disturb you to watch the videos.
  3. Can you understand the content of these videos or not? If not, please indicate it
  4. Did you find any mistake in the video? Pealse indicate it/them.
  5. Can you keep in watching the videos? Why or why not?
  6. Do you think these videos are attractive or boring? Why?
  7. Do you feel the image and of the videos are clear and visual confortable? If not, please indicate the part that you think is not clear and makes you unconforatble.
  8. Does the sound in the videos is clear? If not, please indicate it.
  9. Do you think these video are helpful for you? Please indicate which aspects you think is it

helpful.

10. Do you think the contents in the videos are acceptable? Why or why not?
  11. Do you think the videos is helpful to quit smoking for you? why or why not?
  12. Is there any part you think need to be deleted? Please indicate it.
  13. Is there anything that you think can be added in these video?
- 

#### **S. 3.2.4. Data collection procedures**

A convenient sampling method will be used in the pilot study. These eligible subjects will be invited to participate in the study after telling the purpose of this study. They will be given the option of participating or refusing and will be told that their participation is voluntary without prejudice. Written consent will be obtained from those subjects accepting to receive the interventions.

The subjects' demographic information, smoking characteristics will assessed by the research helpers. Then the ordered video will be sent to the participants through the smart-phone. After watching the video, the participants will be invited to attend a ten minutes invterview, the interview will be guided by research student and tape recorded.

#### **S. 3.2.5. Data analysis**

The feedback comments will be transcribe into the computer and summarized. Then the videos will be modified based on the result of pilot study.

### **S. 3.3. Phase 3: major study**

#### **S. 3.3.1. Study design**

A parallel three-armed cluster randomized controlled trial will be used in this study to explore the efficient of a video-based intervention to the smoking cessation for male smokers preparing for pregnancy.

#### **S. 3.3.2. Sampling**

Male smokers, who met the inclusion criteria for the study in Shenzhen will be invited to participate. The inclusion criteria are: the participants should be (1) male resident aged 18 or above; (2) smoking at least one cigarette per day averagely during the past 1 months (exhaled CO verified); (3) get married and partner has been pregnant (no deformity); (4) able to communicate in Mandarin (including reading Chinese); and (5) have a smartphone for intervention and follow-up. Smokers who meet the above criteria but are currently involved in other smoking cessation programs or the pilot study and/or mentally or physically unfit for communication will be excluded.

Based on previous study conducted in Mainland China, the 6-month quit rate for the control group was approximately 14.8%[60, 61]. According to previous RCT of text message intervention, the rate ratio of quit rate for the intervention and control group was 2.18 (intervention group: 10.7%, control

group: 4.9 %)[62]. To detect a significant difference of quit rate between intervention and control groups with a power of 80 and 5 % significance level, 264 subjects per group will be needed. Assuming an retention rate of 80% at the 6-month follow-up, the total sample size taking into account in the recruitment session and attrition is 990.

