#### *S. 3.3.4.2. Smoking hazard text-messaging+brief advice +Pamphlet*

Text message with the same context with the video will be sent to the participants in the intervention group 2. Also the participants will receive a brief quit advice and pamphlet material related to the smoking cessation at the baseline.

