#### **S. 3.3.7. Data collection procedures**

Male smokers will be recruited in the Obstetrics and Gynecology clinics at tertiary public hospitals in China when the males accompany with their partners to have a body check. Invitation letter will be sent to the public hospitals to participate in this study. After obtain the permission of these hospitals. These eligible people were invited to participate in the study after telling the purpose of this study. They will be given the option of participating or refusing and will be told that their participation is voluntary without prejudice. Written consent will be obtained from those subjects accepting to receive the interventions.

After the consent is obtained, the participant will be coded. By using a computer random selection procedure from the code, the participants will be randomly allocated into three arms, which are intervention group 1, intervention group 2 and control group. The subjects' demographic information, smoking characteristics, self-efficacy level, and exhaled carbon monoxide (CO) level at the baseline will be assessed by the research nurses. The biochemical validation will be done by a staff member who has not delivered the intervention and conducted the telephone counselling follow-up. Yet all subjects will not be blinded, because they will receive the behavioral intervention.

In the intervention group, the smokers will receive an intervention including video, brief advice, and pamphlet. In the intervention group 2, the subjects will text message, brief advice and pamphlet. For the participants in the control group, they will only receive a brief advice and pamphlet materials at the baseline. The detail procedure of data collection is presented in the figure 2 below.

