#### **S. 3.4. Data analysis**

The IBM SPSS Statistics (SPSS: Version 20.0; SPSS Inc., Chicago, IL, USA) for windows will be used for data analysis. A p-value  $<0.05$  was considered as statistically significant. Descriptive statistics will be used to calculate the frequency and percentage (categorical data) or the mean and standard deviations (continuous data) of different demographic and social-economic characteristics. The intention-to-treat (ITT) principle will be used for outcome comparison between groups. Information missed at follow-up will be considered as non-quitters, non-reducers or do not use the video if no records about watching full video set. Multiple imputation will be used to fill the missing value of the demographic information at baseline. One-way ANOVA test or Mann-Whitney test and chi-square test will be used to compare the differences of nicotine dependency, stage of readiness to quit, and self-efficacy among three groups between baseline and 6-month follow-up for those who continued smoking. Logistic multiple regression will be conducted to examine the association between the intervention and the outcomes at 6-month follow-up. Subgroup analysis will be

performed by the first time to be father, level of nicotine dependence, and readiness to quit at baseline.

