#### **S.4. Significance, Expected result and Implementation**

The results of the study can verify the efficient of the video based smoking cessation intervention for the male smokers preparing to pregnancy, and provide essential complementary information on the baseline of self-efficacy about the smoking cessation for male smokers. Besides, result of this study will provide the evidence that a smartphone video is an efficient media which can improve the feasibility of smoking cessation intervention.

The findings from this study can provide information to the health professionals. Then they can adjust the implementation and policy, and further develop appropriate intervention to take fully advantage of family members to help the smokers to quit smoking more efficiently.

Figure 2. The procedure of data collection

[figure not shown]

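### Two active arms share one control, but no primary contrast or test order is named for the 5% level: if both are tested unadjusted, the chance of a false rejection in either direction is about 9%

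*Protocol*

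**What the plan says.** - **Arms.** In S. 3.3.7, "the participants will be randomly allocated into three arms, which are intervention group 1, intervention group 2 and control group". All three receive brief advice and a pamphlet. Group 1 also receives the videos. For the other active arm, "Text message with the same context with the video will be sent to the participants in the intervention group 2" (S. 3.3.4.2).
- **Primary outcome.** S. 3.3.6.1 gives one endpoint, self-reported 7-day abstinence at 6 months. It does not say which arms are compared.
- **Sample size.** S. 3.3.2 aims "To detect a significant difference of quit rate between intervention and control groups" and continues "with a power of 80 and 5 % significance level, 264 subjects per group will be needed". With 80% retention the total is 990. The planning effect, 10.7% against 4.9%, comes from a text-message trial. The same paragraph also says that "the 6-month quit rate for the control group was approximately 14.8"%.
- **Analysis.** In S. 3.4 a p-value below 0.05 "was considered as statistically significant". A logistic regression relates the intervention, in the singular, to the 6-month outcomes. No contrast, order of tests or adjustment is given for the quit rate.
- **Focus.** S. 3.3.1 describes the trial as a study of a video-based intervention, and S.4 says the results "can verify the efficient of the video based smoking cessation intervention". Neither names the comparator.

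**The concern.** The sample size and the significance rule are written for a trial with one intervention group, and this trial has two. The reader cannot tell which comparison owns the 5% level and the 80% power. The design and significance sections point to video, while the planning effect comes from text messaging. If both active arms are compared with control at p<0.05 and either result may be reported as the trial's finding, the 5% level no longer describes the trial as a whole. The choice of which arm carries the conclusion could then be made after the results are seen.

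**Working it through.** **Inputs.** Three arms (S. 3.3.7). Equal allocation, inferred from 264 per group and 990 = 3 × 330. Rates 4.9% and 10.7%, power 80%, level 5%, retention 80% (S. 3.3.2). Threshold p<0.05 (S. 3.4). Participants are treated as independent.

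**1. Reproduce the plan's figure.** For two proportions,

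n = [z_α √(2p̄(1−p̄)) + z_β √(p₁(1−p₁) + p₂(1−p₂))]² / (p₁−p₂)²

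with p₁ = 0.049, p₂ = 0.107, p̄ = 0.078 and z_β = 0.842.

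- One-sided 5%, z_α = 1.645: [1.645 × 0.3793 + 0.842 × 0.3770]² / 0.058² ≈ 263.3, so **264**, an exact match.
- Two-sided 5%, z_α = 1.960: 335.
- 264 / 0.80 = 330, and 330 × 3 = 990, an exact match.
- A control rate of 14.8% with a rate ratio of 2.18 gives 72 (one-sided) or 92 (two-sided), so 14.8% is not behind 264.

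The planned number is therefore one pairwise comparison at one-sided 5%, with no allowance for a second active arm.

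**2. Error if both active arms are tested against control.** With equal arms, each difference has variance 2v and the two share covariance v through the control arm, so the test statistics have correlation 0.5. Suppose no arm differs from any other.

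| Rule for each test | Error counted | One test | Two tests, shared control |
|---|---|---|---|
| Two-sided 5% | Rejection in either direction | 5% | 9.07% |
| Two-sided 5% | False benefit over control | 2.5% | 4.5% |
| One-sided 5% | False benefit over control | 5% | 8.8% |

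The two-test figures come from the bivariate normal distribution. Independent tests would give 1 − 0.95² = 9.75% in the first row, and the Bonferroni bound there is 10%. Simulated binomial data at 264 and 330 per arm, with quit rates of 4.9% and 14.8%, gave 8.8% to 9.1% for that row.

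**3. If video versus text were also confirmatory.** All three pairwise tests at two-sided 5% give 12.2% (studentized range; binomial simulation 11.8% to 12.3%). At one-sided 5% the figure is 12.6%.

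**4. Price of splitting alpha instead.** Halving the level over the two comparisons with control, at the plan's rates:

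| Basis | n per group, full 5% | n per group, halved | Power at 264, full 5% | Power at 264, halved |
|---|---|---|---|---|
| One-sided | 264 | 335 | 80% | 70% |
| Two-sided | 335 | 406 | 70% | 60% |

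**The case against.** The main objection is that contrast ordering and multiplicity rules often sit in a statistical analysis plan, which is not shown here. One comparison at a full 5% is also exactly what a single primary contrast, or a fixed sequence, needs. On that reading S. 3.3.2 is sound, and the video focus in S. 3.3.1 and S.4 already suggests video versus control, with an error of 5%. Part of this stands: the sample size does not contradict the remedy. What remains is that the protocol itself fixes a level, a sample size and a general p<0.05 rule for an unspecified intervention when there are two. The video focus suggests a contrast but does not name it.

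Three stronger readings are tempting, and the protocol does not support them:

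- **That any arm reaching p<0.05 counts as success, so the chance of a false success claim is 9%.** No success rule is written, and the separate tests are inferred from the three arms and the common threshold. The 9% also counts an active arm found worse than control. False benefit is 4.5% with two-sided tests.
- **That 12% is the trial's error rate because S.4 needs video versus text.** The text arm carries the same content, so a claim that the video format beats text would need that contrast. S.4 makes no claim of superiority over text, and video versus control could support what it says.
- **That multiplicity explains a fall in power from the planned 80% to 60%.** The step from 80% to 70% comes from one-sided against two-sided testing, which is a separate matter. Splitting alpha accounts for about 10 points on either basis.

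A significant three-group test on the quit rate, required before any pairwise test, would also hold the error near 5% (4.99% in simulation with no true difference). The three-group tests in S. 3.4, however, are for dependence, readiness and self-efficacy in continuing smokers, not for the primary outcome.

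**Conclusion.** The point holds in conditional form. The protocol does not say which of the two active arms its 5% level applies to, nor in what order the contrasts are tested. If both are tested against control at that level, the chance of at least one false rejection in either direction is about 9%. The chance of a false claim of benefit over control is 4.5% with two-sided tests, or 8.8% at the one-sided 5% that gives 264. About 12% applies only if video versus text is made confirmatory as well, which the protocol does not do.

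These figures assume equal arms, independent participants and no true difference between any arms. S. 3.3.1 calls the trial cluster randomised while S. 3.3.7 describes allocation of individuals; the figures follow the latter. If video versus control were declared the sole primary comparison, the error would be the planned 5%.

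**What to change.** State the following in S. 3.3.2 and S. 3.4:

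1. Video versus control on the 6-month quit rate is the single primary comparison, at 5%, with its sidedness stated.
2. Text versus control is tested at 5%, and is confirmatory only if the first test is significant.
3. Video versus text is either last in the sequence, tested only if both earlier tests are significant, or declared exploratory.

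This order follows the video focus of S. 3.3.1 and S.4. The investigators may prefer another, provided it is fixed in advance.

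The cost is a few sentences. The sample size and the level of the first test stay as they are, whereas splitting alpha on the plan's one-sided basis would need 335 per group instead of 264. The downside is that text versus control cannot be claimed as confirmatory if video versus control fails. The change does not settle whether the 5% behind 264 should be one-sided or two-sided, which needs its own correction.
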